### Study population and sample size

HIV-infected individuals age 18 years or older who are considered stable on ART will be enrolled in the study. The definition of “stable on ART” and other inclusion and exclusion criteria are summarized in Table 1. Since there is no universally accepted definition of stability, criteria were developed for the study based on the expert opinion of infectious diseases specialists. As this is a cluster-randomized trial, study participants will receive the dispensing strategy that was randomly assigned to the cluster (health facility) at which they receive their HIV care.

**Table 1 Tab1:** Study inclusion and exclusion criteria

Inclusion criteria
• Confirmed HIV-1 infection based on country standard of care for testing algorithm
• Stable on ART, defined as:
− on ART for at least 6 months
− on a first-line ART regimen as defined by country-specific guidelines (efavirenz, tenofovir, and emtricitabine or lamivudine)
− no drug toxicity/tolerability issues within the prior 6 months
− no period of more than 1 month without medication possession within the last 6 months
− no active opportunistic infection (OI) suspected (including tuberculosis (TB)) and not treated for an OI within the last 30 days
− undetectable viral load (as defined by country guidelines) within the last 6 months:
▪ Malawi: less than 1000 copies/mL
▪ Zambia: less than 20 copies/mL
• Willing and able to provide written informed consent
• Planning to receive HIV care from the same facility for at least 1 year
Exclusion criteria
• Co-morbid condition(s) for which the individual is treated at the ART clinic (hypertension, diabetes mellitus, chronic lung disease, etc.)
• Pregnant or breastfeeding, or if not breastfeeding, less than 6 months postpartum
• Already receiving care within a differentiated model in which care is received as a group or in a community, such as a community-based adherence group or adherence club
• Enrolled in any other research studies that would influence ART adherence, retention, or dispensing interval

### Sample size

Our study sample size was estimated for a cluster-randomized non-inferiority trial. With 30 clusters available for randomization, we estimated the sample size assuming a fixed number of clusters (*k*), an equal number of clusters per arm, and an equal number of subjects per cluster. Using a one-sided *Z* test (unpooled) with a significance level of 0.05, we estimated that about 5% of subjects would fail to be retained in care in the standard of care arm and 7.5% to be non-inferior in the 3-month or 6-month study arms. Assuming power of 90% and an intracluster correlation coefficient (ICC) of 0.004 [11], we will need to enroll 271 subjects per cluster for a total of 2710 subjects per arm and 8130 total individuals.

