**Methods:**

This study will be an unblinded cluster-randomized, matched controlled trial conducted among 8200 stable, HIV-infected individuals age 18 years and older on ART in Malawi and Zambia, to compare three ART dispensing intervals on the outcomes of retention in care (primary outcome), virologic suppression, and cost-effectiveness. Thirty clusters will be matched according to country, facility type, and ART cohort size and randomized to one of three study arms: standard of care, 3-month dispensing, and 6-month dispensing. Study participants will be followed, and outcomes will be measured at 12, 24, and 36 months. A subset of participants (n = 240) and providers (n = 180) will also participate in qualitative interviews to evaluate feasibility and acceptability of different ART dispensing intervals.

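### The 90% power rests on a normal approximation with only 10 facilities per arm; on the plan's own inputs a t reference gives about 88% when no gain from matching is credited

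*Protocol article*

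**What the plan says.** The protocol article, Sample size, names its method and inputs:

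- Test: "Using a one-sided *Z* test (unpooled) with a significance level of 0.05".
- Expected rate in the control arm: "about 5% of subjects would fail to be retained in care in the standard of care arm".
- Non-inferiority limit for the two intervention arms: "7.5% to be non-inferior in the 3-month or 6-month study arms".
- Power and clustering: "Assuming power of 90% and an intracluster correlation coefficient (ICC) of 0.004".
- Number of facilities: "With 30 clusters available for randomization, we estimated the sample size assuming a fixed number of clusters".
- Balance assumed across arms and facilities: "an equal number of clusters per arm, and an equal number of subjects per cluster".

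The result is 271 per facility, 2710 per arm and 8130 in total. The section mentions no t distribution, no degrees of freedom and no allowance for a small number of clusters. It credits no gain from matching.

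The abstract says that "Thirty clusters will be matched according to country, facility type, and ART cohort size and randomized to one of three study arms". Blinding and allocation adds that one facility of each matched set goes to each arm. Data analysis plans a log-linear GEE with facility-level clustering, robust standard errors and 95% confidence intervals.

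**The concern.** The randomised unit is the facility. A design effect enlarges the variance of the difference between arms, but normal quantiles then treat that enlarged variance as known. In the analysis it has to be estimated from about 20 facilities per comparison, and that uncertainty costs power if the test is to keep its level. The Z formula lands on 271 after rounding up from 270.5, so no slack is left to absorb the cost.

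At stake is the accuracy of a stated operating characteristic. In a non-inferiority trial, lower power means a higher chance of failing to show non-inferiority when the arms are truly equal. If normal critical values are kept instead, the cost appears as a one-sided error above 5%.

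**Working it through.** **Inputs, all from Sample size:** one-sided level 0.05; power 0.90; 5% not retained; limit 7.5%, so margin 0.025; ICC 0.004; k = 10 facilities per arm; equal facility sizes. The true difference is taken as zero. The article does not say so, but this reading reproduces 271. Reading 5% v 7.5% as a difference to detect gives 444 per facility, and a one-sided 0.025 level gives 441.

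**Step 1: reproduce the plan.**
- Individually randomised size per arm: n = (1.645 + 1.282)² × 2 × 0.05 × 0.95 / 0.025² = 1301.7.
- Fixed number of clusters: m = n(1 − ICC) / (k − n × ICC) = 1301.7 × 0.996 / (10 − 5.207) = 270.5, rounded up to 271.
- Design effect: 1 + 270 × 0.004 = 2.08.
- Standard error: √(0.095 × 2.08 / 2710) = 0.00854.
- Standardised margin: 0.025 / 0.00854 = 2.928.
- Z power: Φ(2.928 − 1.645) = 90.0%.

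**Step 2: same inputs, t reference.** Power is the probability that a noncentral t variable with noncentrality 2.928 exceeds the one-sided 5% critical value. No gain from matching is credited.

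| Degrees of freedom | Where they come from | Critical t | Power |
|---|---|---|---|
| 27 | variance pooled over all 30 facilities, matching ignored | 1.703 | 88.7% |
| 18 | two arms, 2 × (10 − 1); also ten matched triplets, (10 − 1) × (3 − 1) | 1.734 | 87.9% |
| 9 | two arms compared as matched pairs | 1.833 | 85.4% |

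At 18 df the shortfall is 90.0 − 87.9 = 2.1 points. The abstract's 8200 participants (8200 / 30 = 273 per facility) give 88.0%, so that rounding does not close the gap. Reaching 90% at 18 df by enrolment alone would take about 322 per facility.

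**Step 3: keep the normal critical value instead.** If 1.645 is used while the variance is estimated on 18 df, the true one-sided error is P(t₁₈ > 1.645) = about 5.9%. The stated 90% and the stated 5% therefore do not both hold without a gain from matching.

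**Step 4: how much matching would be needed.** Split the design effect into its within-facility part, 1 − 0.004 = 0.996, and its between-facility part, 271 × 0.004 = 1.084. At 18 df, power reaches 90% when the between-facility part falls by about 14%: 0.996 + 1.084 × 0.86 = 1.93. The reduction needed is about 9.5% at 27 df and about 29% at 9 df.

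**Step 5: unequal sizes (assumption).** With a coefficient of variation of 0.3 in facility size, the design effect is 1 + (1.09 × 271 − 1) × 0.004 = 2.178, and power at 18 df is 86.6%. The article gives no such coefficient.

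**The case against.** **Nothing is miscalculated.** The article names the Z test openly and its figures reproduce. This stands: the point concerns the choice of reference distribution, not arithmetic.

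**Matching may recover the loss.** A reader might infer that no test holding its 5% level can reach 90% with this design. The article does not support that. Facilities are matched on characteristics chosen because they could predict outcomes, and an analysis by matched triplet still has 18 df. A 14% reduction in between-facility variance would be enough. But the article neither quantifies such a gain nor uses one in its calculation, so it cannot be credited to the stated 90%.

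**The gap is smaller than the uncertainty in the inputs.** With the same 18 df formula, an ICC of 0.003 gives 91.5% and 0.005 gives 84.2%; a non-retention rate of 4.5% gives 90.6%. This is true and limits the importance of the point. Those errors can go either way, though, whereas using Z in place of t always overstates power.

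**Facility sizes may be nearly equal.** Study sites selects facilities partly on their ability to enrol at least 271. This is fair: the 86.6% rests on an assumed spread and should not be read as the trial's expected power.

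**The planned analysis is a GEE with 95% intervals.** An article may leave a small-sample correction to the full protocol or analysis plan, so its absence here is no fault. It also means that 88% applies only to the one-sided 5% risk-difference comparison in Sample size. If a two-sided 95% interval decided non-inferiority, the same inputs would give about 83% (Z) or 79% (t, 18 df).

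**Conclusion.** The point holds as a modest overstatement of power. On the plan's own inputs, with equal facility sizes and no gain from matching, power for the one-sided 5% comparison is about 88% (87.9% at 18 df; 85.4% to 88.7% across the plausible degrees of freedom). The chance of missing true non-inferiority is then about 12%, where the plan implies 10%.

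A reader might go further and conclude that the trial certainly lacks 90% power. The article does not show that, because the gain from matching is unknown. What it shows is that the calculation offered for 90% does not allow for estimating the between-facility variance from 10 facilities per arm. The design is not undermined and the sample size need not change.

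**What to change.** 1. Keep 271 per facility. In Sample size, replace the Z reference with a t reference on cluster degrees of freedom, and state power as about 88% for the one-sided 5% comparison (18 df, equal facility sizes, no matching gain credited). If the sponsor has a defensible figure for the matching gain, state it and recompute.
2. Use the same cluster-level degrees of freedom for the GEE inference with robust standard errors, so that the 5% level assumed in the sample size holds in the analysis. If the full protocol or analysis plan already does this, a cross-reference is enough.
3. If unequal facility sizes are mentioned, give about 87% as a sensitivity figure, labelled as resting on an assumed coefficient of variation of 0.3.

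The cost is a few sentences and a slightly less favourable stated power. No participants, facilities or procedures are added.

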### Study procedures and data collection

The study procedures and data collection methods are described in detail below. A summary of the study visits and evaluations is outlined in the SPIRIT Figure (Fig. 2) below.

**Fig. 2 Fig2:**
[figure not shown]
SPIRIT Figure. *Default defined as out of antiretroviral therapy (ART) for more than 60 days; ^&^Zambia only; ^^^Malawi only; CPT: co-trimoxazole prophylaxis therapy; IPT: isoniazid preventive therapy

#### Eligibility screening

Patients will be provided general information about the study in ART clinic waiting areas and recruited by a study staff representative. Interested patients will be taken to a private space with a study staff representative to learn about the study, provide oral consent, undergo anonymous screening procedures, and, if eligible, provide written informed consent. A recent viral load test (within 6 months of the entry visit date) is required to determine eligibility; however, we anticipate many participants will not have a recent viral load result available at the time of screening. For participants who do not have a viral load documented, a sample will be collected after written informed consent is obtained, but the participant will not be enrolled in the study until the test results have been received. Patients who have a viral load sample drawn for study eligibility will receive test results during their next routine visit and will repeat the screening survey at that visit to ensure there have been no changes in eligibility criteria over the interim period.

#### Entry visit data collection

All patient baseline data will be collected in the entry visit, which may come immediately after screening for eligible patients, or may take place at the next visit when a viral load result is available. Two types of data will be collected at the entry visit. First, the participant’s medical record will be reviewed to collect clinical history, including date of HIV diagnosis, date of ART initiation, use of CPT and/or IPT, and history of ART clinic visits and ART dispensing intervals in the prior 12 months. The second type of data will come from an interview with the patient. In the interview, the study interviewer will obtain sociodemographic information about the participant, including gender, highest level of education, household composition, employment status, HIV disclosure status, and travel and opportunity costs related to the participant’s ART clinic visits. After completion of the entry visit data collection, the participant will complete her or his routine clinic visit with site providers and receive ART dispensing as per the site randomization. If CPT and/or IPT dispensing is standard of care for the facility, CPT and/or IPT will also be provided as per the randomized dispensing interval.

#### Follow-up data collection

Retention and virologic suppression will be assessed 12, 24, and 36 months after the entry visit date. At each of these time points, data from participants’ medical records will be collected by study staff. Data will include number, timing, and reason for clinic visits, retention in care (and if not retained, reason), possession of ART based on number of pills dispensed at each visit, possession of CPT and/or IPT based on number of pills dispensed at each visit, and viral load. Study staff will allow up to 60 days after a time point has been reached before medical record review, allowing for participants to meet the protocol-defined definition of default. For participants who default, facility standard of care procedures for tracing may be used, but the study will not make contact with the participant for the purposes of facilitating return to care.

#### Qualitative data collection

To help understand patients’ and providers’ perceived feasibility and acceptability of the dispensing intervals offered in the study, qualitative, semi-structured, in-depth interviews will be conducted at the study sites for both patients and providers after the 12-month primary endpoint has been reached. For study participants, a subset (up to 40 from each arm in Malawi and another 40 from each arm in Zambia, or a total of up to 240 individuals) will be randomly selected to participate in an individual, in-depth, qualitative interview. Participants will only be contacted for an interview if they provide informed consent for future contact at the time of initial written informed consent. Those who agree to an interview will return to the clinic for this step and will be reimbursed transport costs for this study visit. The interview will be conducted in a private room at the clinic in a local language and will last approximately 1 hour. Participants will be asked about their experiences receiving their assigned dispensing interval, including challenges in transporting medications from clinic, challenges in storing medications at home, pressure to sell or give ART supply to others, clinic usage outside of ART refills, and perceived financial challenges that result from clinic visits.

There is a possibility that the interviews may influence participants’ future outcomes in the study, particularly retention in care. Patients may change their behavior as a result of more intensive contact with study staff, because of being reimbursed for a study visit, or as a result of information discussed in the interview. The total number of individuals participating in interviews is less than 3% of the total study population, and these individuals will be excluded from outcome analyses after the first year.

We will also collect qualitative data from a subset of providers (n = 30) drawn from lists provided by the study sites from each of the three study arms in each country (total n = 180). These interviews will be performed after 50% of the facility’s study participants have reached the 12-month endpoint. For providers who agree to participate, study staff will complete an anonymous screening survey to determine eligibility to participate in the interview. If eligible, providers will be asked for written informed consent. The interviews will be conducted in English in a private space at the facility. Questions will focus on provider perceptions of challenges faced by patients in transporting or storing medications; perceptions of the degree to which patients lose, sell, or give away ART; issues related to medication stock and storage within their facility; and perceptions about the effect of ART dispensing interval on clinic efficiency and health system costs.

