### Data analysis

#### Primary outcome

Our primary outcome, which is the basis for our sample size estimates and primary analysis, is retention in care at 12 months after study enrollment. Data analyses will begin with descriptive measures about the study population stratified by treatment arm and by facility and presented as medians and interquartile ranges for continuous measures and proportions for categorical variables. These measures will be used to look for large variations by facility and for imbalances between study arms.

We will perform an intention-to-treat analysis for the primary outcome of retention. Our analysis will use a log-linear generalized estimating equation to estimate the risk ratios and associated 95% confidence interval for the effect of each intervention arm compared to standard of care. We will specify facility-level clustering to account for the study design and estimate robust standard errors using an unstructured correlation matrix. Should we identify any baseline imbalances between study arms, we will adjust for these in our multivariable model and report adjusted risk ratios and corresponding 95% confidence intervals.

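### Participants who took part in an interview are left out of the 24- and 36-month outcome analyses, so the exclusion depends on retention-related behaviour; the effect is small and the 12-month primary analysis is untouched

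*Protocol article*

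**What the plan says.** The section on qualitative data collection sets out the steps. Interviews are held "after the 12-month primary endpoint has been reached". The number is "up to 40 from each arm in Malawi and another 40 from each arm in Zambia, or a total of up to 240 individuals". A subset "will be randomly selected to participate in an individual, in-depth, qualitative interview", with a condition: "Participants will only be contacted for an interview if they provide informed consent for future contact", and that consent is given at entry. "Those who agree to an interview will return to the clinic for this step".

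The same section gives a reason for caution: more contact with staff, reimbursement of the visit, or the content of the interview might change later behaviour, retention above all. It then says that "The total number of individuals participating in interviews is less than 3% of the total study population" and that "these individuals will be excluded from outcome analyses after the first year".

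Elsewhere in the article:
- The Background lists retention at 12, 24 and 36 months as the primary outcomes.
- The primary outcome section under Data analysis makes 12 months the basis of the sample size and the primary analysis, and adds: "We will perform an intention-to-treat analysis for the primary outcome of retention".
- The data safety and monitoring plan lets a difference at 12 or 24 months between 3- and 6-month dispensing stop the study.
- The secondary outcomes section repeats cost per patient retained at 24 and 36 months.

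**The concern.** The group left out is described as the individuals participating in interviews. That is not the same as the group drawn at random. Someone drawn who cannot be reached, refuses or does not come back stays in the denominator at 24 and 36 months; someone who comes back leaves it. Willingness and ability to return to the clinic after month 12 is closely tied to being retained, so the rule selects on a relative of the outcome. The random draw does not cure this, because the selection happens after the draw.

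At stake are the absolute retention rates at two of the three time points that the Background calls primary, the 24-month comparison that can feed the stopping rule, and the cost per patient retained at the later time points.

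**Working it through.** **Inputs from the article.** Per arm N = 2710 (10 clusters of 271); 8130 in total, rounded to 8200 in the Abstract; up to 40 interviewees per arm and country, so up to 80 per arm and 240 overall; 5% non-retention, 2.5-point margin, one-sided 0.05, 90% power, ICC 0.004.

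**Inputs assumed.** Non-retention p at 24 and 36 months, and retention r among interviewees. The article gives neither, so ranges are shown.

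**1. The plan's own figures.**
- Interview share: 240/8130 = 2.95%, or 240/8200 = 2.93%. The statement of less than 3% is right.
- Sample size: 1302 per arm without clustering; with k = 10 clusters, m = 1302 × (1 − 0.004)/(10 − 1302 × 0.004) = 270.6, rounded up to 271. This gives 2710 per arm and 8130 in total, as stated.

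**2. Effect on one arm's rate.** With 80 interviewees removed, the analysed rate is

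p′ = (N·p − 80·(1 − r))/(N − 80).

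The upper bound is r = 100%, where p′ = p × 2710/2630 = 1.0304·p:

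| Assumed p | p′ at r = 100% | p′ at r = 98% | p′ at r = 95% |
|---|---|---|---|
| 5% | 5.15% | 5.09% | 5.00% |
| 10% | 10.30% | 10.24% | 10.15% |
| 15% | 15.46% | 15.40% | 15.30% |
| 20% | 20.61% | 20.55% | 20.46% |

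The relative inflation is at most 3.04%. It is zero when interviewees are retained exactly as well as the arm as a whole, as the cell for 5% and r = 95% shows.

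**3. Effect on the comparison, equal numbers per arm, r = 100%.** Take 5% and 7.5% as the true rates.
- Ratio of non-retention: 7.73/5.15 = 1.50, unchanged.
- Ratio of retention: 0.9737 becomes 0.9728.
- Difference: 2.50 points becomes 0.025 × 2710/2630 = 2.58 points.

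**4. Unequal numbers, for scale only.** If 80 took part in one arm and 40 in another, with the same true rate and r = 100%, a difference appears that is not real. At 5% it is 135.5/2630 − 135.5/2670 = 0.08 points; at 10% it is 271/2630 − 271/2670 = 0.15 points.

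**5. Precision.** Removing 8 per cluster (80/10) lowers power under the design assumptions from 90.0% to 89.6%.

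**The case against.** The strongest reply is that the protocol made a disclosed choice between two small biases. Suppose interviewees would otherwise have had 10% non-retention and the interview cut this to zero. Keeping them would then lower the arm's rate by 80 × 0.10/2710 = 0.295 points, about the same size as the 0.30-point inflation above and opposite in sign. This stands as an argument against treating full retention of the sample as free of cost. It does not rescue an exclusion by participation. Excluding everyone drawn removes all interviewees, and so any interview effect, without selecting on who came back.

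A second reply is that the primary analysis is at 12 months, before the interviews, and that the intention-to-treat sentence follows that definition. That is right for the primary analysis. The Background nevertheless names all three time points as primary outcomes, and the stopping rule can use 24-month data, so the later analyses deserve the same principle.

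A third reply is that a sensitivity analysis may sit in the full protocol or analysis plan. Its absence from the article is not the point; the point is the exclusion rule that the article does state.

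One ambiguity should be granted. The article uses 240 both for those drawn and for those interviewed, and does not say whether people who decline are replaced. The natural reading is still that those interviewed are excluded.

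A reader might go further and infer that interview uptake will differ by arm, because one arm attends half as often, and so bias the comparison. The documents do not support this. The cap is the same for each arm and country, the section on the intervention describes the interviews as evenly balanced among the arms, and the interview is a separate, reimbursed visit that does not depend on refill attendance.

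**Conclusion.** The point holds as a minor one. The stated rule excludes by participation, which follows allocation and is related to retention, and so departs from intention to treat at 24 and 36 months. The direction of bias rests on interviewees being retained better than average. That is plausible, but the documents give no figure, and a person seen shortly after month 12 still has 12 to 24 months in which to default. It would therefore go too far to treat interviewees as almost entirely retained: the 3% relative inflation (10% to 10.3%) is an upper bound and not an expected value.

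Nor should a reader conclude that the trial's main result is threatened. The 12-month analysis is unaffected. With equal numbers per arm the risk ratios, which are the planned measure, barely move, and the change on the difference scale is 0.08 points beside a 2.5-point margin. What is left is a slight distortion of the later absolute rates and a departure from principle that can be avoided cheaply.

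**What to change.** Keep all enrolled participants in the main 24- and 36-month intention-to-treat analyses. Examine whether interviews changed behaviour in an additional analysis that excludes everyone randomly drawn for interview from those who consented at baseline to future contact, whether or not they took part. If the sponsor prefers an exclusion in the main analysis, define it by the draw and not by participation. In either case record the drawn list, including anyone drawn as a replacement, and make the draw without regard to whether the person was still in care at month 12.

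The cost is a sentence or two in the analysis plan and one extra analysis. No new data are needed, because later outcomes come from medical records. The downside of keeping everyone is possible slight reactivity in up to 3% of participants. The downside of excluding the drawn set is the loss of about 3% of the sample, or more if people who decline are replaced.
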